#### Sample identification

Once a school has agreed to be a trial school then the trial team will support them to identify whole classes that have students that meet the eligibility criteria. We will work with schools to assess how best to deliver *Lina* within the routine school day, i.e. identify a specific subject or class that could integrate the intervention and be part of the regular school day. As an example, in the UK it is likely that the intervention will be delivered as part of Personal, Social, Health and Economic (PSHE) lessons which covers a range of topics related to personal development. However, schools can individually choose where they think *Lina* best fits within their curriculum.

The variation of subjects and lesson content both across schools and across countries means that the trial team will take a pragmatic approach to delivery and support the schools in making tailored decisions. It is recommended to schools that each of the six *Lina* sessions is delivered weekly for 6 weeks within a single term. However, due to the pragmatic nature of the trial, and the understanding that schools (both within and between countries) structure lessons in different ways, schools may choose to deliver the sessions at different frequencies or across shorter or longer time periods (e.g. some schools may choose to deliver two sessions of *Lina* a week for 3 weeks). The variation in delivery will be collected as the observational data and form part of the analysis. Irrespective of the intervention delivery, follow-up outcome measures will be collected at 8–10 weeks after baseline.

#### Interview and focus group sampling

Purposive sampling will be used to identify individuals of interest to participate in the planned post-trial interviews and focus groups (that make up part of the implementation evaluation and exploration of lived experiences).

For young people, individual interview data will be collected from particularly vulnerable students, who want to talk about *Lina* (i.e. have something to say), and have characteristics that make them more likely to have relatively extreme (good or bad) experiences of *Lina*. Focus group data will be collected from students who want to talk about *Lina*, for example because they have had a particularly good or bad experience of *Lina.* In the UK, the vulnerable students for interviews will be defined by three separate criteria: (i) recipient of pupil premium, (ii) having special educational needs and disabilities (SEND) and (iii) having experienced “notable social experiences” e.g. negative experiences like bullying and/or positive social experiences such as being part of an extracurricular club or society outside of school. Students will have the opportunity to self-identify with (any of) these characteristics and teachers will also be asked to recommend students. In PT and CZ, students for interviews will be identified based on discussion with teachers. In all countries, students will be given the opportunity to self-select for focus group participation, and students may also be recommended by teachers or by observing researchers.

For teachers—all teachers who facilitated the use of *Lina* will be invited to attend an interview or focus group.

## Assignment of interventions: randomisation

### Sequence generation: who will generate the sequence {21a}

#### Randomisation scheme

The trial will employ a cluster randomised design, with class being the unit of randomisation. Whole classes will be randomised to either the *Lina* arm or the control group arm.

The trial statistician at Queen Mary University of London will use STATA to randomise a list of classroom IDs to either intervention or control conditions. IDs will then be assigned to classes in the order in which they are enrolled.

Classes within schools will be randomised at the same time (where possible) and the school and individual teachers will be informed of their allocation by the local research assistant or the trial manager.

### Sequence generation: type of randomisation {21b}

Randomisation will be stratified by country, and then stratified by blocks of 2 or 4. The randomisation scheme may be amended as and when the full list of participating trial schools is known. Any future amendment to the randomisation scheme will be there to ensure that there is at least one class in the *Lina* arm per school (important for school retention) and to ensure that there are comparable numbers of participants randomised to each of the trial arms.

Randomisation will occur only when: schools have agreed to be part of the trial; appropriate classes that meet the inclusion criteria have been identified; adolescents have agreed to the study and all students have been allocated to the class. Once these terms have been met then randomisation can be triggered. Randomisation will occur before participant baseline data collection. The allocation ratio will be 1:1.

### Allocation concealment mechanism {22}

Due to the nature of the trial, allocation concealment can only be maintained at the level of data collection. To ensure allocation concealment, password-protected randomisation allocation lists generated by the statistician will be maintained in Excel files and shared only with the Trial Manager and unblinded researchers in each trial team responsible for intervention scheduling. Passwords for the excel sheets will be communicated via a secure separate channel and deleted afterwards to prevent accidental disclosure to blinded researchers responsible for facilitating trial assessments. Logs containing any data linking classroom-level information to concealment will be restricted to unblinded researchers until the end of the trial assessments (e.g. post-intervention and 6-month follow-up).

### Implementation {23}

As the unit of randomisation in this trial is the classroom, all students within participating classrooms will be enrolled into the trial, provided they have met the relevant consent criteria. The procedure is listed below:The trial team in each country will be responsible for enrolling eligible classrooms within recruited schools.A list of classroom IDs will be produced and shared with the Trial Statistician who will generate the allocation sequence using block randomisation (blocks of two and four) to assign classrooms to intervention or control arms. IDs will then be assigned to classes in the order in which they are enrolled.

## Assignment of interventions: blinding

### Who will be blinded {24a}

#### Blinding

Due to the nature of the intervention under investigation and the cluster design of the trial, blinding participants (and teachers) to their allocation will not be possible. Baseline data will be collected post-randomisation, but prior to the start of the intervention. Participants in the class will not be informed of allocation prior to baseline data collection (although teachers will be aware due to pragmatic considerations around lesson planning, for example).

In the UK trial, researchers facilitating the baseline, post-intervention and 6 months follow-up will be blinded to allocation where possible.

Due to researcher capacity in Portugal and Czechia, blinding will not be possible at any of the post-intervention follow-ups (i.e. T1 and T2).

The statistician and health economist will be unblinded to allocation at the time of analysis. Neither analyst will have involvement in data collection, intervention delivery nor allocation concealment and their roles will begin once the database is locked and the randomisation sequence is revealed. As recent literature suggests, there is limited benefit of blinding the statistician at data analysis if allocation concealment is maintained during data collection [45]. To further minimise the risk of analytical bias, the statistical analysis plan (SAP) will be finalised and signed off by the Trial Steering Committee before database lock and commencement of analysis, specifying all primary and pre-planned sensitivity analyses.

### How will be blinding be achieved {24b}

Blinded researchers will be determined prior to the start through the Trial Delegation log. To avoid any unblinding, efforts will be made to ensure that unblinded researchers are not responsible for coordination, allocation information will be stored separately from assessment material, will be password-protected and masked in any analysis datasets until the primary analysis is completed.

### Procedure for unblinding if needed {24c}

Unblinding researchers to participant allocation may occur in the interest of participant safety e.g. if the knowledge of the participant’s allocation is necessary for the appropriate management of an adverse event or severe adverse event. Any such request would be formally documented in a trial file note, and reported to the Principal Investigator and Trial Manager.

## Data collection and management

### Plans for assessment and collection of outcomes {25a}

All outcome measures used have been validated for use with adolescents. The list of outcome measures was decided upon thorough consultation with the Trial Management Group (TMG) and a panel of young co-researchers (see heading 12 for full list of outcome measures).

#### Data collection for outcome measures

Electronic case report forms (e-CRF) will be created to collect socio-demographic data and outcome data (separate versions for each timepoint) (these can be accessed on the ASP*belong* Open Science Framework project page [46]). The e-CRFs will be hosted on smartphone-compatible software that will link to the online trial database (REDCap) through a unique participant number. At baseline, a record will be created in the database for each participant. Following baseline data collection, an individual URL will be created by the REDCap software for each participants’ data row. At post *Lina* and follow-up data collection timepoints, a bespoke application (built by the project team) will open the e-CRF linked to the correct URL when the corresponding participant number is entered. Participants will complete the measures on the smartphones provided by the study team (the same devices used to deliver the intervention). In the event of technical challenges with electronic data entry (e.g. Wi-Fi issues), paper forms will be used to complete the assessment.

e-CRFs will be completed as part of the routine school day, within a class session. They will be collected from all consenting students within that class at the same time, facilitated by the class teacher or a psychologist (PT) and a researcher (UK, CZ), who will offer support where needed around understanding questions in a consistent manner within each country context (i.e. explaining certain terminology within item wording that students query). If a participant is absent from school, or data is missing for any reason, then the research team will have 3 weeks from the data collection time point to collect that data.

### Plans to promote participant retention and complete follow-up {25b}

We will not be collecting any individual-level contact information for participants except where necessary to coordinate data collection for people actively opting into interviews and/or focus groups. Efforts for participant retention and mitigating attrition will therefore be on a school-level. We have worked on establishing strong relationships with schools and teachers through regular communication, several networking opportunities, and emphasising a strong sense of collaboration. Further, we will be flexible with scheduling lessons to accommodate the academic calendar/exam time, or any other school events.

No data will be collected from students who withdraw themselves or whose parents withdraw them from the trial. Furthermore, in the event that a student was to leave the school or be transferred to a different class within the same school during the intervention, they would cease to receive the intervention, and no further data would be collected from them.

### Data management {26}

The primary mode of data capture will be through electronic Case Report Forms (e-CRFs) administered on smartphones via REDCap (Research Electronic Data Capture) which is a secure, web-based system designed for building and managing research data. If REDCap is unavailable (e.g. device malfunction, connectivity issues), paper Case Report Forms (CRFs) will be used. Paper CRFs will be entered into REDCap at the earliest opportunity, with the paper copy stored securely at each site in a locked cabinet and stored separately from any identifiable enrolment information. Each participant survey will be linked to a unique participant ID (PID), and the follow-up assessments are linked to it. Paper-based data can be transferred between individual sites (e.g. schools) to the central site but will never leave the central site (e.g. University of Birmingham in UK, Masaryk University in CZ and Académico Torres Vedras (ATV) in Portugal). Access to the REDCap portal will be granted to designated and trained researchers at each site for the manual data entry of paper CRFs into the online portal. Site leads and researchers will be responsible for first-level quality control of the data entry and checks. The trial manager will oversee routine monitoring and any data errors in the database will be queried and resolved with the relevant site team. Once data is entered into REDCap, data exports can be produced through reports for data verification and analysis by the Trial Statistician.

### Confidentiality {33}

The trial will comply with the requirements of the UK Data Protection Act 2018, as standard, with regard to the collection, storage, processing and disclosure of personal information and will uphold the Act’s core principles throughout the study, and be UK General Data Protection Regulation (GDPR) compliant. As all trial data (from all three countries) will be stored in the UK, the relevant national legislation of the UK will be followed:

All data will be confidential at the point of collection, linked to participants via unique ID numbers. Identifying information (participant full names and contact details) will only be collected for participants (students and teachers) in the qualitative and implementation evaluations, and only when necessary (e.g. to arrange data collection with a student, which may otherwise be arranged via the class teacher). Personal information will be stored in password-protected spreadsheets at the local research site (University of Birmingham, Masaryk University, Académico Torres Vedras) and linked to research data via the unique ID.

Interviews and focus groups (qualitative and implementation evaluations) will be audio recorded and these data will be potentially identifying. Recordings will be stored securely at each research site until transcription, when any potentially identifying information will be removed (transcripts will be anonymous). Following verification of the transcripts, the audio data will be deleted. Only anonymous data will be shared across research sites for analysis.

## Statistical methods

### Statistical methods for primary and secondary outcomes {27a}

#### Statistical analysis

Data for the three trials will be analysed separately (by country), before later being pooled for overall analysis.

Participant level socio-demographic data and cluster level (classroom) data will be summarised at baseline for both arms of the trial.

The primary outcome is the Delaware Class Climate score at the end of *Lina* delivery (8–10 weeks post baseline and follow-up). This will be compared between *Lina* and control groups using a linear mixed effects model with a random effect for classroom and school, allowing for the clustering of children, within classes, and within schools. The model will include baseline level of the Delaware Class Climate as a covariate, as well as demographics (that are known to affect outcome). The analysis will use intention to treat by including all participants in the arm to which they were randomised, whether or not they completed the *Lina* programme and including all students in the analysis by using multiple imputation. We will set out in the statistical analysis plan (SAP) how missing data will be handled, including planned sensitivity analyses.

Secondary outcomes are WHO-5, PHQ-8, SAS-A, UCLA Loneliness Scale, SSIS SELb, PMHSS-R, EQ-5D-Y-3L and CHU-9D all measured at post-intervention (T1) and 6 months post baseline (T2). Each variable will be analysed using a generalised linear mixed effects model with a link function appropriate to the outcome distribution, with random effects for classroom and school. All models will include the baseline value of the outcome.

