## Intervention and comparator

### Intervention and comparator description {15a}

#### Description of the intervention

The intervention under investigation *Lina* is a newly developed software-led program with accompanied in-person reflection designed to enhance students’ sense of belonging through a blended approach of interactive gameplay facilitated by smartphones in a classroom setting. All necessary equipment, including smartphones, routers, headphones and paper-based materials will be provided by the trial team to the class.

The intervention is primarily user-driven but will be guided by the classroom teacher (or a psychologist in the case of PT). Additionally, a researcher will be present during every session to make observational notes and support usage, where required. The intervention consists of six sessions. Four of these are “episodes” of the *Lina* story and will be delivered on a provided individual smartphone, while two will be “analogue” sessions, which are structured and interactive sessions within the classroom to enhance the sense of belonging and embed the psychotherapeutic principles inherent in the intervention. In CZ and the UK, it is typically teachers who will deliver the analogue sessions, in line with detailed lesson plans and provided materials. In PT the psychologist members of our team will deliver these sessions, in line with national legislation.

The order will be as follows:

Lesson 1: *Lina* episode 1.

Lesson 2: *Lina* episode 2.

Lesson 3: Analogue session 1.

Lesson 4: *Lina* episode 3.

Lesson 5: *Lina* episode 4.

Lesson 5: Analogue session 2.

During the smartphone-based sessions, each student plays a character in a fictional class. The four *Lina* episodes follow the story of a girl called Lina, a fictional classmate who abruptly left the school. Lina had been secretive, and at times, Lina’s behaviour seemed unusual or difficult to understand. The class collectively decides to uncover what happened to her. Players examine objects Lina left behind using augmented reality, revisit shared memories and piece together the story. By the last episode, they learn that Lina has been caring for her mother, who struggles with a poor mental health (low mood, guilt) that has profoundly affected their daily lives. Lina and her mother have moved to live with Lina’s aunt, allowing her mother to receive support while Lina returns to her previous school.

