### Sample size {19}

#### Size of trial sample

Based on an assumed small to medium effect size (Cohen’s *d* = 0.4) based on school mental health meta-analyses [43], and a conservative Intraclass Correlation Coefficient (ICC) of 0.1 [44], which takes into account the clustering at the class and school level, and a design effect of 2.7, 40 classes per country will provide 90% power (alpha = 0.05).

The analysable trial sample assumes an average cluster size of 18 (a total of 720 participants per country). To allow for an anticipated drop-out rate of 20%, an average cluster size of 22 will be recruited at baseline (i.e. average 22 adolescents per classroom), thus giving a total sample size of 880 per country. The cluster size of 22 at baseline takes into account the variability in class sizes within and across each country, and expected number of participants who opt out of the study.

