#### Size of interview and focus group sample

For the post-trial interviews and focus groups it is predicted that there will be a maximum of 160 young people per country invited to participate in the evaluative qualitative work (up to 120 young people invited to a focus group, and 40 young people invited to be interviewed).

For teachers, there is predicted to be 20 teachers per country eligible to be interviewed or invited to a focus group.

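### Portugal: Lina is delivered by trial-team psychologists who probably each serve several classes, and neither the class-and-school model nor the 90% power allows for this one-arm clustering

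*Protocol article*

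**What the plan says.** The Trial design section has teachers facilitating Lina in Czechia and the UK and a psychologist delivering the sessions in Portugal, for regulatory reasons. The intervention description says of the two analogue sessions: "In PT the psychologist members of our team will deliver these sessions, in line with national legislation". It also describes the programme as mainly driven by the users, with the teacher or psychologist in a guiding role.

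Under Statistical analysis, one model is given for the separate country analyses of the primary outcome: a "linear mixed effects model with a random effect for classroom and school, allowing for the clustering of children, within classes, and within schools". The secondary outcomes use the same random effects. No term refers to the person delivering Lina.

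The sample size section uses one calculation for all three countries. It has an "assumed small to medium effect size (Cohen’s *d* = 0.4") with a "conservative Intraclass Correlation Coefficient (ICC) of 0.1 [44], which takes into account the clustering at the class and school level". It states the design effect as 2.7 and concludes that "40 classes per country will provide 90% power (alpha = 0.05"). Allocation is 1:1, so about 20 Portuguese classes receive Lina.

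The protocol gives neither the number of Portuguese psychologists nor the number of classes each one takes.

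**The concern.** When one person delivers an intervention to several clusters, those clusters share whatever that person does well or badly. Here the sharing would exist only in the Portuguese Lina arm, because control classes have no psychologist. A class random effect treats classes as independent, and a school intercept is common to both arms, so neither absorbs an effect that is shared across Lina classes alone.

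Sharing is not stated, but it is likely. The psychologists belong to the trial team, Portugal has a single centre, and the blinding section says researcher capacity there (and in Czechia) is too limited for blinded follow-up assessment. Such a team is unlikely to supply a separate psychologist for each of about 20 classes.

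At stake are the width of the Portuguese confidence interval, its false-positive rate and its power. These matter because the Portuguese trial is to be powered and analysed on its own.

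**Working it through.** **Inputs from the protocol:** d = 0.4 (SD 1), ICC 0.1, 18 analysable students per class, 40 classes per country at 1:1. This gives 20 classes and 360 students per arm. Alpha is 0.05, taken as two-sided.

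**Inputs assumed, because the protocol gives none:** K psychologists sharing the 20 Lina classes equally, and a psychologist share ρ of total outcome variance, counted inside the ICC of 0.1.

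**1. The stated power.** Design effect = 1 + 17 × 0.1 = 2.7. Variance of the difference = 2 × 2.7/360 = 0.0150, so SE = 0.1225. Power = Φ(0.4/0.1225 − 1.96) = 90.4%. The stated 90% therefore reproduces from class and school clustering alone and holds no allowance for psychologists.

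**2. Adding shared psychologists.** The planned model in effect spreads the psychologist variance over 20 independent classes (ρ/20). The actual contribution is ρ/K. Equivalently, the Lina-arm design effect becomes 2.7 + (360/K − 18)ρ, and

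true SE / modelled SE = √[(Lina-arm design effect + 2.7)/5.4].

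Type I error is 2 × [1 − Φ(1.96/ratio)]. Power with the true SE is Φ(0.4/(0.1225 × ratio) − 1.96).

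**3. Worked case, K = 3 and ρ = 0.02.** Lina-arm design effect = 2.7 + 102 × 0.02 = 4.74. Ratio = √(7.44/5.4) = 1.174. True SE = 0.1438. Type I error = 9.5%. Power = Φ(2.78 − 1.96) = 79.5%.

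**4. Range.**

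| K | ρ | SE ratio | Type I error | Power |
|---|---|---|---|---|
| 2 | 0.02 | 1.265 | 12.1% | 73% |
| 2 | 0.05 | 1.581 | 21.5% | 54% |
| 3 | 0.02 | 1.174 | 9.5% | 79.5% |
| 5 | 0.02 | 1.095 | 7.4% | 85% |
| 6 | 0.005 | 1.019 | 5.4% | 89% |
| 10 | 0.005 | 1.008 | 5.2% | 90% |
| 10 | 0.05 | 1.080 | 7.0% | 86% |
| 20 | any | 1.000 | 5.0% | 90.4% |

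If ρ is added on top of the ICC of 0.1, the K = 3, ρ = 0.02 case gives 78% power and the same type I error.

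**5. Simulation.** Class means were simulated with 10 schools of 4 classes, school as a block, and 4,000 runs per case. For K = 3, ρ = 0.02 the mean reported SE was 0.116 against an empirical 0.140, with type I error about 10%. With ρ = 0, or one psychologist per class, type I error stayed near 5%.

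**6. Baseline adjustment.** The stated 90% ignores the baseline covariate. Assume that baseline explains 25% to 36% of the variance at student and class level and none of the psychologist effect. For K = 3, ρ = 0.02 the non-psychologist variance is 0.0150 − 0.02/20 = 0.0140 and the psychologist part is 0.02/3 = 0.00667.

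- At 25%: 0.0105 + 0.00667 = 0.01717, SE 0.131, power 86%. The planned model would report a variance of 0.0105 + 0.001 = 0.0115, so type I error is 10.9%.
- At 36%: 0.00896 + 0.00667 = 0.01563, SE 0.125, power 89%. The planned model would report 0.00996, so type I error is 11.8%.

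The baseline covariate can thus restore most of the stated power, but it does not remove the type I inflation.

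All power figures use a normal reference. With very few psychologists, a test with suitable degrees of freedom would have less power than shown.

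**The case against.** The strongest objection is that the size rests on two quantities the protocol does not give. With one psychologist per class, or no variation between psychologists, nothing is wrong. The extreme of 22% needs two psychologists holding half of an ICC that the protocol already calls conservative. Four of the six sessions run on the smartphone, which may leave little room for a psychologist effect. This stands, and it is why the point is conditional. It does not remove the gap, because two sessions are led in person and the outcome includes classroom-relationship subscales.

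The inflation also depends on the estimand. For Lina as delivered by these particular psychologists, the class-and-school standard error is not understated. That is correct. However, the Discussion justifies psychologist delivery by its relevance to long-term use in Portugal, so readers will want to generalise.

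The SAP is not shown and may add such a term. The random-effects structure and the power figure are nevertheless already stated in the protocol, and nothing there signals a Portuguese exception.

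Three stronger readings are tempting and not supported:

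- A reader might infer that the Portuguese standard error is definitely too small. The documents do not state that psychologists are shared or that their effects differ.
- A reader might infer from "For teachers, there is predicted to be 20 teachers per country eligible to be interviewed or invited to a focus group" that each UK and Czech Lina class has its own teacher. That sentence predicts eligibility for interviews and focus groups in all three countries and says nothing about classes per teacher.
- A reader might infer that Portugal would be over-weighted in the pooled result. The pooled analysis is described only as one dataset with a country level, and no effect on its weights has been shown.

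**Conclusion.** The point holds in conditional form. The Portuguese trial has a probable level of clustering, by psychologist and in the Lina arm only, that neither the stated model nor the stated power covers. Under 2 to 6 psychologists and a 0.5% to 5% variance share, type I error for inference beyond these psychologists would be about 5% to 22%. With 3 psychologists and 2% it is about 10%, with power near 80% before baseline adjustment and about 86% to 89% after it under the assumptions shown. With about 10 psychologists or a negligible effect, little changes. It is worth acting on because the change is cheap, not because an error has been demonstrated.

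**What to change.** 1. Record a psychologist ID for every Portuguese Lina class. Session logs and observation forms already exist, but the protocol does not say that they identify the deliverer, so this field may have to be added or reconstructed.
2. State the number of psychologists and the number of classes each one took.
3. In the SAP, before database lock, add to the Portuguese analysis a psychologist random effect that applies to the Lina arm only (a partially nested model) with small-sample degrees of freedom. Report it beside the class-and-school model.
4. If there are too few psychologists to estimate that variance, about five or fewer, show the Portuguese effect by psychologist and limit the conclusion to Lina as delivered by them.
5. Describe the Portuguese 90% power as assuming no psychologist clustering, and give a range over plausible numbers of psychologists and variance shares.

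The cost is one ID variable and some SAP wording. The Portuguese interval becomes somewhat wider and its stated power less favourable. The conduct of the trial does not change.
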